All children will then be treated according to the standard management protocols of that particular clinic. It is expected that some of the study children with pneumonia will go on to develop severe pneumonia, and require hospital referral. If this should happen the local health worker will ensure that the child is referred to the nearest health facility to receive medical care. A detailed record of the treatment given to the caregiver will be recorded.

It is recognized that children attending a clinic with pneumonia could represent a biased group that are not fully representative of all sick children. We will collect DHS data on socio-economic status in order to compare the sample population to a wider population. Furthermore, it is possible that the consent process and information sheet may introduce a source of bias in the recording of recall of symptoms and events.

*Follow up at home*

The primary caregivers of these children will first be interviewed using the DHS and MICS questions relating to pneumonia (see Annex) either at 2 weeks (200 with pneumonia and 200 with cough or cold) or 4 weeks (100 with pneumonia and 100 with cough or cold) after diagnosis. This will follow the DHS and MICS procedures as closely as possible. The order of administering the DHS and MICS questionnaires will be alternated with each child so that each is administered first on 50% of occasions. After this is completed they will then also be questioned about specific signs of pneumonia (which will form a pneumonia score - see below) and will be asked to watch a video of a child suffering from pneumonia and of a child suffering from an upper respiratory infection (asking which best represents their child’ respiratory illness episode). Finally, a drug chart will then be used to show them pictures of locally used medicines with a request to identify which medicines, if any, their child was prescribed. These research workers should be given the address details of the child but not be made aware of the study group of the child nor have access to the clinical details of the child recorded at recruitment.

*Home visit interview sequence:* The research worker will

1. introduce him/herself to the caregiver, and check that the details match those on the recruitment form.
2. inform the mother of the interview process and ensure that she is willing to participate (and obtain written consent).

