3. check that the child’s details are correct, and make sure that the caregiver understands that the interview only concerns this child, and that she should only answer the questions in relation to this child.
4. start by asking the DHS questions (Annex 1) then ask MICS questions (Annex 2) – this sequence will be alternated from child to child to that DHS is asked first in 50% of children
5. ask pneumonia score questions (Annex 3)
6. show the caregiver the video clips and ask mother to identify which disease best represents her child
7. show the caregiver a drugs chart and ask her to identify with what her child was treated; note whether treatment information is based on this or actual observation of medications in the home
8. ask if the mother has a pharmacist’s note or a ‘road to health’ card, and record any information from the past 2 or 4 weeks.

*Study analysis*

The study report will include a detailed description of the epidemiological and health services characteristics of the study population

There will be 4 separate groups interviewed in this study:

- Mother’s whose child has been accurately diagnosed as having pneumonia (or severe pneumonia if this is treated in the community) by a physician, and is interviewed after 2 weeks.
- Mother’s whose child has been accurately diagnosed as having pneumonia (or severe pneumonia if this is treated in the community) by a physician, and is interviewed after 4 weeks.
- Mother’s whose child has been accurately diagnosed as not having pneumonia by a physician, and is interviewed after 2 weeks
- Mother’s whose child has been accurately diagnosed as not having pneumonia by a physician, and is interviewed after 4 weeks

Data from the interviews and the clinical case study forms will be used to calculate sensitivities and specificities of each of the above methods (DHS / MICS defined pneumonia; pneumonia defined by various pneumonia score thresholds; video-assisted recognition of pneumonia) for the diagnosis of pneumonia and for antibiotic treatment. These will be estimated for all possible pneumonia score thresholds so that an optimum performance threshold can be defined for the score. The caregiver will then be asked to show the research worker any pharmacist’s note, ‘road to health’ card or other health record which may have details of the illness and treatment given.

*Sensitivity + specificity calculations:*

|  | | **Medical diagnosis of Pneumonia** | | |
| --- | --- | --- | --- | --- |

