**NOTES**

*Pneumonia score:*

A set of 10 items from a list of 20 possible questions will be selected at each study site (based on what local doctors / researchers consider to be most culturally appropriate and based on the findings of the pilot study - selected by the local PI based on level of comprehension by caregivers, performance in comparison to known diagnoses and the informed opinion / experience of the local PI). This list represents symptoms and signs of pneumonia which are of increasing severity. The interviewer will ask the caregiver about the presence of each specific sign separately, and record her responses. The clinical signs are:

- Cough
- Fever
- Sweating
- Irritability
- Fatigue
- Restlessness
- Fast breathing
- Shortness of breath
- Loss of appetite
- Decreased water intake / drinking
- wheezing
- Chest pain
- Difficulty breathing
- Intercostal or subcostal retractions
- Flared nostrils
- Grunting
- Repeated vomiting
- Cyanosis
- Haemoptysis / blood when child coughs
- Fits

*Video clips*

During the interview, the research worker will show the caregiver a short video clip showing a child suffering from pneumonia, followed by a clip showing a child with a “cough or cold”. The videos will show clinical signs commonly associated with both, and the mother will be asked which clip most accurately shows the signs her child was displaying when they were ill. The research worker will record whether the caregiver selected the child with pneumonia, or the child with “cough or cold”.

- Child with signs of pneumonia: clinical signs of pneumonia (fast breathing of at least 10-15 breaths /minute above the threshold for that age and /or chest indrawing)
- Child with signs of “cough or cold”: (blocked or runny nose and noisy upper respiratory breathing but NO fast breathing at least 10 breaths /minute below the age threshold)

There should be a video made of a 2 month old child and a 2 year old child for both pneumonia and “cough and cold”. An alternative to be explored in the pilot study is to make separate videos of children with “cough and cold”, pneumonia (fast breathing) and severe pneumonia (chest indrawing). The research worker should select the age category that will best represent the child which is being recruited and show the relevant clips to the mother.

*Drug Chart*

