**Annexes:**

**Annex 1: DHS(V) questions – these will be replaced by the MEASURE DHS phase III questions (in related document “Copy of DHS6 Woman's QRE 16 March pneumonia-1”**

533 *Has (NAME) been ill with a fever at any time in the last 2 weeks?*

*Yes 1*

*No 2*

*Don’t Know 8*

1. *Has (NAME) had an illness with a cough at any time in the last 2 weeks?*

*Yes 1*

*No 2*

*Don’t Know 8*

1. *When (NAME) had an illness with a cough, did he/she breathe faster than usual with short, rapid breaths or have difficulty breathing?*

*Yes 1*

*No 2*

*Don’t Know 8*

1. *Was the fast or difficult breathing due to a problem in the chest or to a blocked or runny nose?*

*Chest Only 1*

*Nose Only 2*

*Both 8*

*Other _______________ (Specify) 6*

*Don’t Know 8*

1. *Check 533: Had Fever?*
2. *Now I would like to know how much (NAME) was given to drink (including breastmilk) during the illness with a (fever/cough). Was he/she given less than usual to drink, about the same amount, more than usual to drink?*

*If less, probe: Was he/she given much less than usual to drink or somewhat less?*

*Much Less 1*

*Somewhat Less 2*

*About the Same 3*

*More 4*

*Nothing to Drink 5*

*Don’t Know 6*

1. *When (NAME) had a (fever/cough), was he/she given less than usual to eat, about the same amount, more than usual, or nothing to eat?*

*If less, probe: Was he/she given much less than usual to eat or somewhat less?*

*Much Less 1*

*Somewhat Less 2*

*About the Same 3*

*More 4*

*Stopped Food 5*

*Never Gave Food 6*

*Don’t Know 6*

1. *Did you seek advice or treatment for the illness from any source?*

*Yes 1*

*No 2*

1. *Where did you seek advice or treatment? Anywhere else?*

*Probe to identify each type of source and circle the appropriate code(s).*

*If unable to determine if a hospital, health center or clinic is public or private medical, write the name of the place.*

*(Name of place)*

*Public Sector*

*Govt Hospital A*

*Govt Health Center B*

*Govt Health Post C*

*Mobile Clinic D*

*Fieldworker E*

*Other Public F*

*________________ (specify)*

*Private Medical Sector*

*PVT Hospital/Clinic G*

*Pharmacy H*

*PVT Doctor I*

*Mobile Clinic J*

*Fieldworker K*

*Other Private Med. L*

*________________ (specify)*

*Other Source*

*Shop M*

*Traditional Practitioner N*

*Other X*

*________________ (specify)*

1. *Were did you first seek treatment? Use letter code from 541.*

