**Annex 2: MICS questions**

| CA7. At any time in the last two weeks, has (name) had an illness with a cough? | Yes 1  No 2  DK 8 | 2CA14  8CA14 |
| --- | --- | --- |
| CA8. When (name) had an illness with a cough, did he/she breathe faster than usual with short, rapid breaths or have difficulty breathing? | Yes 1  No 2  DK 8 | 2CA14  8CA14 |
| CA9. Was the fast or difficult breathing due to a problem in the chest or a blocked or runny nose? | Problem in chest 1  Blocked or runny nose 2  Both 3  Other (specify) 6  DK 8 | 2CA14  6CA14 |
| CA10. Did you seek any advice or treatment for the illness from any source? | Yes 1  No 2  DK 8 | 2CA12  8CA12 |
| CA11. FROM WHERE DID YOU SEEK ADVICE OR TREATMENT? |  |  |
| CA12. Was (name) given any medicine to treat this illness? | Yes 1  No 2  DK 8 | 2CA14  8CA14 |
| CA13. What medicine was (name) given?  Probe:  Any other medicine?  Circle all medicines given. Write brand name(s) of all medicines mentioned.    (Names of medicines) | Antibiotic  Pill / Syrup A  Injection B  Anti-malarials M  Paracetamol / Panadol / Acetaminophen P  Aspirin Q  Ibuprofen R  Other (specify) X  DK Z |  |

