**Annex 3:** **Pneumonia score questions**

*1 Has (name) suffered from a* ***cough*** *in the past (___) weeks?*

*2 Has (name) had a* ***fever*** *in the past (___) weeks?*

*3 Has (name) suffered form* ***chills or sweats*** *over the past (___) weeks?*

*4 Has (name) been* ***restless*** *over the past (___) weeks?*

*5 Has (name) been unusually* ***irritable*** *over the past (___) weeks?*

*6 Has (name) had any* ***loss of appetite*** *over the past (___) weeks?*

*7 Has (name) been* ***abnormally sleepy*** *or* ***difficult to wake*** *over the past (___) weeks?*

*8 Have you noticed (name) making a* ***wheezing*** *sound when he/she breathed over the last (__) weeks?*

*9 Has (name) appeared* ***short of breath*** *over the past (___) weeks?*

*10 Has there been a period over the past (___) weeks when (name) has seemed to be* ***breathing faster*** *than normal?*

*11 Have you noticed (name’s)* ***nostrils flaring*** *when he/she breathed over the past (___) weeks?*

*12 Has (name)* ***refused to drink*** *or had a definite* ***decrease in the amount of water he / she drank*** *over the past (___) weeks?*

*13 Did you notice that (name’s)* ***skin between their ribs, or his/ her tummy move inwards*** *when they breathed over the past (___) weeks*

*14 Did (name) seem to have any* ***chest pain*** *over the past (___) weeks?*

*15 Has there been a period over the last (___) weeks where (name) seemed to have* ***difficulty breathing****?*

*16 Has (name)* ***vomited*** *at all over the past (___) weeks?*

*17 Have you heard (name) making* ***grunting*** *noises during the past (___) weeks?*

*18 Has (name) appeared to have a slightly* ***blue coloration*** *to his/her skin, particularly their lips or tongue, over the past (___) weeks*

*19 Has (name)* ***coughed up any blood*** *over the past (___) weeks?*

*20 Has (name) had any* ***fits*** *overt the past (___) weeks*

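### The pneumonia score items are tied to a span of weeks, not to the respiratory illness, so signs from separate illnesses add into one score

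*Protocol*

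**What the plan says.** Annex 3 lists 20 score questions, of which each site selects 10. Every one is framed by a past or last number of weeks, left blank. Item 10 on fast breathing opens "Has there been a period over the past (___) weeks when (name) has seemed to be", and item 16 reads "Has (name)* *vomited* *at all over the past (___) weeks". None mentions the cough illness or the clinic visit. The list in the NOTES, from which the score is built, has the narrower sign "Repeated vomiting".

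The other tools are worded differently. MICS question CA8 in Annex 2 asks "When (name) had an illness with a cough, did he/she breathe faster than usual with short, rapid breaths or have difficulty breathing", and the breathing question printed in Annex 1 for DHS has the same form. The video step, as described under Follow up at home, works by "asking which best represents their child’ respiratory illness episode". Step 3 of the home visit interview sequence has the caregiver told that "the interview only concerns this child, and that she should only answer the questions in relation to this child"; it limits answers to the child, not to an illness.

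The reference standard is a physician's diagnosis at one clinic visit. The score is cross-tabulated against it at every threshold, and ROC curves are used to choose the cut-off. Accuracy is then compared between caregivers interviewed at 2 and at 4 weeks.

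**The concern.** A score built this way need not describe one illness. Fever from one episode and vomiting from another count towards the same total, which is then judged against a diagnosis made on a single day. A child correctly classified as having a cold can reach the cut-off because of something unrelated.

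Two planned results are affected. The first is the score's sensitivity, specificity and ROC cut-off, and with them the comparison against DHS, MICS and the video. The second is the 2- versus 4-week comparison. The blank is never fixed, but the natural reading is the follow-up interval, since step 8 of the home visit uses the past 2 or 4 weeks for written records. The 4-week group would then have twice as long to collect unrelated signs. A window equal to the interval also lies mainly after the diagnosis, with the diagnosed illness at its edge.

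**Working it through.** The protocol states no figure on this point to reproduce. The check sets the wordings side by side, derives the direction, and then sizes the effect under assumptions.

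**Wording**

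| Tool | What the sign is tied to | Window |
| --- | --- | --- |
| Score (Annex 3) | the child only | blank number of weeks |
| MICS CA7 and CA8 (Annex 2) | any cough illness | last two weeks |
| DHS breathing question (Annex 1, as printed) | any cough illness | last two weeks |
| Video | the respiratory illness episode | none stated |
| Reference | physician diagnosis | one clinic visit |

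**Direction.** Let S be the number of items positive because of the diagnosed illness, U ≥ 0 the extra items positive because of another illness, and c the cut-off. The recorded score is S + U. Among children without pneumonia, P(S + U < c) ≤ P(S < c), so specificity can only fall. Among children with pneumonia, P(S + U ≥ c) ≥ P(S ≥ c), so apparent sensitivity can only rise. With memory held equal, a longer window can only increase U.

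**Size, illustration (a).** Specificity = Sp0 × [1 − q × (1 − exp(−λ × weeks))]. Sp0 is 0.70 to 0.90, the baseline range in the sample size section. λ, new illnesses per child-week, and q, the chance that such illness lifts a sub-threshold child over the cut-off, are assumptions.

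| Sp0 | λ | q | 2 weeks | 4 weeks | Further loss |
| --- | --- | --- | --- | --- | --- |
| 0.70 | 0.05 | 0.25 | 0.683 | 0.668 | 1.5 points |
| 0.80 | 0.10 | 0.50 | 0.727 | 0.668 | 5.9 points |
| 0.90 | 0.20 | 0.50 | 0.752 | 0.652 | 9.9 points |

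Middle row: 0.80 × [1 − 0.50 × (1 − exp(−0.2))] = 0.727 and 0.80 × [1 − 0.50 × (1 − exp(−0.4))] = 0.668.

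**Size with forgetting, illustration (b).** Take ten independent items and a cut-off of 5, the protocol's example. Assume that each item is positive from the diagnosed cold with probability 0.30, that unrelated signs occur at b per item per week, and that a fraction r of the cold's signs is still reported at 4 weeks (all at 2 weeks). Then p2 = 1 − 0.70 × (1 − b)², p4 = 1 − (1 − 0.30r) × (1 − b)⁴, and specificity = P(Binomial(10, p) ≤ 4).

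| b | r | 2 weeks | 4 weeks |
| --- | --- | --- | --- |
| 0.01 | 1.0 | 0.825 | 0.798 |
| 0.02 | 1.0 | 0.798 | 0.742 |
| 0.05 | 1.0 | 0.710 | 0.557 |
| 0.02 | 0.9 | 0.798 | 0.800 |
| 0.02 | 0.8 | 0.798 | 0.851 |

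At b = 0.02, p2 = 1 − 0.70 × 0.9604 = 0.328. With r = 1, p4 = 1 − 0.70 × 0.9224 = 0.354; with r = 0.9, p4 = 1 − 0.73 × 0.9224 = 0.327. Ten per cent forgetting hides the wording effect and twenty per cent reverses the observed change. The data would show only the sum.

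**The only illness rates in the protocol.** The General Introduction gives clinical pneumonia at 0.36 per child-year for South-East Asia and an upper quartile of 0.71 across studies. With 1 − exp(−rate × weeks/52), these give 1.4% and 2.7% of children with a new episode in 2 weeks, and 2.7% and 5.3% in 4 weeks.

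**The case against.** A reader might infer that DHS and MICS are tied to the diagnosed illness, so that new episodes harm only the score. The documents do not support that. The MICS gate question CA7 and its DHS counterpart accept any cough illness in the last two weeks. A cold-group child who later develops a cough with fast breathing becomes a false positive there too. As printed, at a 4-week interview those questions reach back only half way to the clinic visit. What survives is narrower: their breathing items do not pool signs from non-cough illnesses, and the score does. The DHS contrast is also provisional, because Annex 1 is to be replaced by questions held in another document.

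A second tempting reading is that score specificity will be seen to fall at 4 weeks. That does not follow, because forgetting removes positive answers. Nor does the protocol say that a fall would be attributed to memory. It asks whether accuracy differs, and for a household survey contamination by other illness is part of how a long window performs. That is fair for operating accuracy, but the research question is put in terms of caregiver recall, and the wording mixes the two.

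Third, size. Items are yes/no and every enrolled child already had acute respiratory symptoms, so a second cough often adds nothing.

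Finally, the wording is provisional: the pilot informs the final score, forms are finalised afterwards, and item 16 may not be among a site's ten. But the stated remit of the pilot is face validity, cultural fit, local terms and item choice. Nothing directs anyone to tie items to the illness, and a minimum of 5 children per group could not show the effect.

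**Conclusion.** The wording defect stands and nothing else in the protocol cures it. Its own effect at a fixed cut-off has a certain direction: specificity no higher, apparent sensitivity no lower. Growth from 2 to 4 weeks depends on the blank being the follow-up interval, and it cannot then be separated from memory effects.

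The size is an assumption. Illustration (a) gives about 1.5 to 10 points of extra specificity loss from 2 to 4 weeks, up to the order of the 10-point difference for which the study is sized. The pneumonia incidence figures cannot stand in for it: they count children exposed rather than specificity lost, and such episodes usually involve cough, so MICS largely shares them. Item 16 is a separate, plain inconsistency with the NOTES. The change is worth making before the forms are finalised.

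**What to change.** - Reword the Annex 3 items so that each refers to the respiratory illness for which the child was seen at the clinic. For survey use, where no clinic visit is known, tie each sign to the cough illness, as CA8 does; this still lets in a second cough illness.
- Give any reminder of that illness after step 4 and before the score at step 5. Placed at step 3 it would cue the DHS and MICS questions being validated. It should mention the clinic visit but no diagnosis, which keeps the interviewer blind.
- Reconcile item 16 with the repeated vomiting listed in the NOTES.
- Add one closing yes/no question, after all others, on whether a new illness began after the clinic visit. Report score accuracy with and without those children as a sensitivity analysis.

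The cost is wording on forms not yet final and one extra question, with no added visits or children. The interview is slightly longer, and some caregivers may not separate the episodes cleanly.

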**Annex 4:** **DRAFT** **Form to be completed by Physician**

Section 1: patient details

Child’s Name (full): ………………………………………........................................

Age: …………………………………………………………………………………...

D.O.B: ………………………………………………………………………………...

Mother’s/

primary caregiver’s name: ………………………………………………......................

Address: ……………………..................

……………………..................

……………………..................

……………………..................

……………………..................

Date of examination:………………………………………………………………....

Section 2: presenting signs + symptoms

Respiratory symptoms: ……………………………………………………………...

……………………………………………………………..

……………………………………………………………..

Respiratory rate:

Temperature (oC):

Sub-costal retractions / lower chest wall indrawing (y/n):

Record any findings on auscultation -

Section 3: Investigation

Chest X-ray ordered (y/n):

Section 4: Diagnosis

Pneumonia non-pneumonia (circle appropriate)

Presence of exclusion criteria

- - recurrent wheezing
  - chronic cough (more than 10 days)
  - already on antibiotic treatment
  - recent pneumonia episode within past 10 days
  - history of congenital heart disease
  - symptoms for more than 4 weeks
  - previous clinic treatment for this illness episode

Section 5: Treatment (to be adapted for each site)

| *Drugs* | | *Please tick those prescribed* |
| --- | --- | --- |
| *Antimalarial Drugs* | *SP/Fansidar* |  |
|  | *Chloroquine* |  |
|  | *Amodiaquine* |  |
|  | *Quinine* |  |
|  | *Combination with Artemisinin* |  |
|  | *Country Spec. CBD Antimalarial* |  |
|  | *Other Antimalarial* | **Specify:** |
|  |  |  |
| Antibiotic Drugs | *Pill/Syrup* |  |
|  | *Injection* |  |
|  |  |  |
| Other Drugs | *Aspirin* |  |
|  | *Acetaminophen* |  |
|  | *Ibuprofen* |  |
|  | *Other* | **Specify:** |

Physician name:………………………………..

Date:……………………………………………

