**Project research questions**

- What is the sensitivity and specificity of the MEASURE DHS PHASE III and MICS questionnaires for caregiver recognition of pneumonia (compared to an expert physician gold standard diagnosis)?
- What are the equivalent estimates of sensitivity and specificity when using an amended survey tool which incorporates:
  - a pneumonia score?
  - video illustrations of signs of pneumonia presented to caregivers?
- What is the sensitivity and specificity of the MEASURE DHS PHASE III and MICS questionnaires for caregiver recall of antibiotic treatment in children with and without pneumonia? (compared to an accurate record of treatment made at time of prescription)?
- What are the equivalent estimates of sensitivity and specificity when using an amended survey tool which incorporates:
  - A paper-based “pill/medicine board” illustrating different locally available treatment options
  - A computer based “pill/medicine board” illustrating different locally available treatment options
- Is there a significant difference in the accuracy of caregiver recall of diagnosis or antibiotic treatment between the 2 weeks and 4 weeks follow up protocol?

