**Table 1: Characteristics of the study sites**

| **Pakistan Urban** |  |
| --- | --- |
| *Geographic Location:* | Islamabad |
| *Principal Investigator:* | [name] |
| *Subcontracting Institution:* | Children’s Hospital, Pakistan Institute of Medical Sciences, Islamabad, Pakistan. |
| *Strategy for recruitment of children with pneumonia:* | Pneumonia cases identified at PIMS, a major children’s hospital by a trained doctor |
|  |  |
| **Bangladesh Rural** |  |
| *Geographic Location:* | Four rural villages: Mirzapur, Gorai, Bhatgram, Jamurki |
| *Principal Investigator:* | [name] [name] |
| *Subcontracting Institution:* | ICDDR,B |
| *Strategy for recruitment of children with pneumonia:* | Pneumonia cases identified at local government health services by a trained doctor |

*Recruitment at clinic*

Children aged 0 to 5 years who present to a health clinic or hospital out-patient department suffering from acute respiratory symptoms will be eligible to be recruited into the study. The children will be assessed according to a standard protocol by a study doctor and key clinical and treatment details recorded. A diagnosis of pneumonia, severe pneumonia or of “cough or cold” (no pneumonia) following an agreed clinical classification system and details of all treatment prescribed will be carefully recorded. Children presenting primarily with an episode of recurrent wheeze (reactive airways disorder / asthma) or who have pneumonia severe enough to require hospital admission or who have symptoms of more than 4 weeks duration or who have already received treatment from health services for the current illness episode will be excluded (so as to limit recall bias associated with the admission).

A detailed address will be recorded and consent sought for a follow up visit. The study will aim to recruit and follow up successfully 300 children with pneumonia (or severe pneumonia if this is treated in the community) and 300 with “cough or cold” (no pneumonia) at each study site. An attempt will be made to recruit all children with pneumonia who present during the defined study period when a trained clinical researcher is available. Children with “cough or cold / no pneumonia” will be frequency matched to pneumonia cases so that in any one week the age and sex distribution of cases of pneumonia and “cough or cold” are similar.

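### The recruitment text and the draft physician form list different exclusions and neither is said to govern; separately, antibiotic recall is scored only against the study-visit prescription

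*Protocol*

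**What the plan says.** Eligibility is stated in two places.

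- **Recruitment at clinic (below Table 1).** It excludes children presenting mainly with recurrent wheeze, those whose pneumonia needs admission, and those "who have symptoms of more than 4 weeks duration". On earlier treatment, children "who have already received treatment from health services for the current illness episode will be excluded".
- **Annex 4, Section 4 (draft physician form).** It lists recurrent wheezing, "symptoms for more than 4 weeks" and "previous clinic treatment for this illness episode". It also lists "chronic cough (more than 10 days", "already on antibiotic treatment", pneumonia in the preceding 10 days and congenital heart disease. It has no item for pneumonia needing admission.

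For antibiotic recall, the Project research questions define accuracy as "compared to an accurate record of treatment made at time of prescription". The treatment table in Annex 4, Section 5 is headed "Please tick those prescribed", so it captures what was prescribed at the study visit. The interview questions are wider. Annex 1 (DHS) asks about drugs taken at any point in the illness, and Annex 2 (MICS, CA12 and CA13) asks about any medicine given for it. Neither limits the answer to the study clinic. The DHS list of care sources includes both pharmacies and shops.

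**The concern.** There are two linked but separate problems.

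First, a recruiting doctor who follows the text and one who follows the form will not accept the same children. Results are to be reported by site and then summarised over sites, so the protocol should fix one population.

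Second, the reference standard for antibiotic recall covers a narrower exposure than the questions being validated. The caregiver is asked about the whole illness, and the answer is checked against one prescription. Where a child took an antibiotic from another source and none was prescribed at the visit, a correct answer is counted against the questionnaire. Specificity of antibiotic recall is one of the project outcomes, and it would look worse than it is.

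The two meet at one point. The text lets in some children already taking antibiotics, and the form would keep them out.

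**Working it through.** **Step 1. The two lists side by side**

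| Item | Recruitment at clinic | Annex 4, Section 4 |
| --- | --- | --- |
| Recurrent wheeze | excluded if the main presentation | excluded |
| Pneumonia needing admission | excluded | not listed |
| Symptoms over 4 weeks | excluded | excluded |
| Cough over 10 days | not listed | excluded |
| Earlier treatment for this episode | excluded if from health services | excluded if from a clinic |
| Already on antibiotics | not listed as such | excluded, any source |
| Pneumonia in preceding 10 days | not listed | excluded |
| Congenital heart disease | not listed | excluded |

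Four items appear only on the form and one only in the text. On cough, a child otherwise eligible with 11 to 28 days of cough passes the text and fails the form, a window of 28 − 10 = 18 days. On antibiotics, the text already removes children treated by health services, a term it does not define. The DHS source list puts pharmacies in the private medical sector and shops under other sources. On that reading the clear gap is shop or other informal supply, and pharmacy purchase is ambiguous.

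**Step 2. How a truthful answer is scored**

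Take a child enrolled under the text while taking a shop-bought antibiotic and prescribed none at the visit. The reference is no antibiotic. The caregiver, asked about the whole illness, truthfully says yes. The child falls in cell b of the protocol's two-by-two treatment table, a false positive.

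**Step 3. How large the effect could be**

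The plan has no figure on this to reproduce. Inputs:

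- Se = 60–70% and Sp = 70–90%, the baseline values in the Sample size calculation. That section does not say whether they refer to diagnosis or to treatment recall, so they serve as illustration.
- f, the share of children with no antibiotic on the visit record who in fact took one from elsewhere. The documents give no value; 2% to 20% is assumed.

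Apparent specificity = (1 − f) × Sp + f × (1 − Se). The loss is therefore f × (Se + Sp − 1).

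| Sp | Se | Se + Sp − 1 | f = 5% | f = 10% | f = 20% |
| --- | --- | --- | --- | --- | --- |
| 70% | 60% | 0.30 | 68.5% | 67% | 64% |
| 70% | 70% | 0.40 | 68% | 66% | 62% |
| 90% | 60% | 0.50 | 87.5% | 85% | 80% |
| 90% | 70% | 0.60 | 87% | 84% | 78% |

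The losses are 1.5–3 points at f = 5%, 3–6 at 10% and 6–12 at 20%. At f = 2% they are 0.6–1.2 points. The planned precision is ±5 points.

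**The case against.** **The lists do not really conflict.** A reader might infer that the two lists contradict each other outright. They do not. Apart from the missing admission item, the form mainly repeats or tightens the text. A 10-day limit on cough and a 4-week limit on any symptom can both be applied. What stands is that the lists differ and nothing says they are to be applied together.

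**The form is a draft.** Annex 4 is marked as such, and forms are finalised after training and pilot. Site visits are meant to finalise the protocol and keep the sites comparable. Within Annex 4, only the treatment section is marked for local adaptation. A reader might infer that the two sites will enrol different populations; the documents show only that they could. This lowers the severity. It does not settle the matter, because finalising the form does not amend the recruitment text.

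**The list mismatch does not cause the mis-scoring.** This is right for the most part. The cause is a prescription-only reference set against whole-illness questions. Adopting the form's rule would reduce the error but not remove it: a finished course, or an antibiotic obtained elsewhere after the visit, would still be mis-scored.

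**Relevant data are already collected.** The drug chart interview asks the source of each medication, and step 8 of the home visit collects pharmacist's notes and health cards. These could identify outside antibiotics, but the protocol does not make them part of the reference.

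**Conclusion.** The point holds as two modest faults: an unreconciled pair of exclusion lists, and a reference for antibiotic recall that is narrower than the questions it validates. The first is certain from the text. The mechanism of the second is also certain on the annexed questions, with one caveat: Annex 1 says its DHS questions will be replaced by a later set that is not shown. Annex 2 carries no such note.

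The size of the second is not known. The 1.5–3, 3–6 and 6–12 point losses rest wholly on assumed shares of 5%, 10% and 20%. Only children who were enrolled, prescribed no antibiotic and supplied from elsewhere count towards f, so 20% is a demanding assumption. With f near 10% the loss is of the same order as the planned ±5 points; at 2% it is negligible.

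A reader might infer larger losses by multiplying 90% by (1 − f), giving 85.5%, 81% and 72%. That takes the top of the specificity range and assumes that every such caregiver reports the antibiotic. The protocol's own 60–70% sensitivity does not support that assumption.

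**What to change.** 1. Reconcile the two exclusion lists into one, and use it word for word in Recruitment at clinic and on the physician form at both sites. Define health services in it. The clinical limits themselves are for the investigators to settle.
2. Add a field to Annex 4 recording antibiotic use in this illness before the visit, from any source.
3. State how children with such use, if enrolled, enter the antibiotic-recall tables: either left out, or with that use counted in the reference.
4. Use the medication source, pharmacist's notes and health cards already collected at the home visit to identify antibiotics obtained elsewhere after the study visit, and say so in the analysis section.

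The cost is wording, one form field and a smaller denominator in the recall tables if children are left out. As an illustration, suppose all 300 cough-or-cold children at a site were prescribed no antibiotic (an assumption). Then 5% to 20% is 15 to 60 children. Even at 60, the confidence interval for specificity widens only by a factor of √(300/240) = 1.12.
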